##### Additional comments

No removal of the stents is contemplated due to the malignant condition of the participants. Non-inpatients, they will remain in the center for a minimum of 24 h for clinical observation under clinical supervision.

In case of technical failure for any reason, alternative strategies will be decided upon with the aim of offering the best possible treatment to the patient.

#### Clinical evaluation and follow-up

##### Data collection and calendar

The collecting of clinical information of the patients will begin at the outset (baseline) and will continue with follow-up as established and defined in the study. Data will be collected at baseline visit, indexing procedure 24 hours later, and at days 14, 30, 90, 180, 270, and 1-year post-randomization. Collected data include primary, secondary, and additional endpoint data, demographics, comorbidities, oncological data, laboratory test findings, technical details, and clinical data during follow-up (Figs. 1 and 2).

**Fig. 2 Fig2:**
[figure not shown]
BAMPI trial Flowchart. DPS double-pigtail plastic stent, ERCP endoscopic retrograde cholangio-pancreatography, EUS-BD endoscopic ultrasound-guided biliary drainage, EE-LAMS, electrocautery-enhanced, lumen-apposing metal stent

AEs will be noted from the beginning of the test until the conclusion of follow-up by means of scheduled controls and will be handled and treated in accordance with the directives of the patient’s medical team. All additional tests and interventions will be duly documented. Any instances of death during the follow-up will be investigated to rule out possible relation to the endoscopic procedure. Such occurrences will also be recorded in the CRF.

If there is clinical suspicion of obstruction or migration of the stent, an upper endoscopy will be carried out. Based on the findings of this procedure, the problem will be resolved in accordance with the directives of the intervening endoscopist. Any additional procedure or endoscopic intervention will be duly documented.

All data will be collected by research personnel knowledgeable in the use of the eCRF (data capturing software, redCAP). Collected patient data will be de-identified, meaning that personal information will not be stored in the main database. All data will be stored for 7 years after publication or as requested in standard operating procedure from individual sites. Only data relevant to the study as outlined in this protocol will be collected by the research team.

Due to the social and health crisis arising from the SARS-CoV-2 pandemic and taking into account the likely frailty of the candidates to be enrolled in the study, the protocol contemplates restrictions on physical presence visits. Only the indexing procedure and the 24-h post-procedure visits will require an on-site visit since a minimum one-day hospital admission is mandatory.

A BAMPI trial flowchart is provided (Fig. 2).

#### Definitions

Technical success is defined as successful placement of the stents (LAMS, DPS, or both) between the extrahepatic bile duct and gastrointestinal lumen by endoscopy, endosonography, and, optionally, fluoroscopy.

Clinical success is defined according to the TOKYO criteria as a 50% decrease in or normalization of total serum bilirubin level within 14 days of index procedure (stent placement). For cholangitis without obstructive jaundice (e.g., segmental cholangitis, cholecystitis), success can be defined as cessation of antibiotics or a 50% decrease in or normalization of levels of blood inflammatory markers within 14 days of stent insertion [20].

RBO is defined as a composite endpoint of stent dysfunction (either occlusion or migration). See Table 2 (outcomes) for complete information [20].

**Table 2 Tab2:** Primary and secondary endpoints

**Primary endpoint:** - Rate of recurrent biliary obstruction (RBO) between the two strategies (LAMS with and without coaxial DPS), detected during follow-up. *RBO is associated with a stent dysfunction (an endpoint of either occlusion^a^ or migration^b^). Tokyo criteria - Clinical recurrence (jaundice, fever, suspicious colangitis, pruritus). - Recurrence of cholestasis parameters (Any increase in GGT/ALP or bilirubin from its lowest level post-index procedure). Both WITH evidence of biliary obstruction on imaging (dilation on US/CT/MRI) or endoscopic findings suggesting it ^c^.	
**Secondary endpoints:** - Technical success defined as successful stents (LAMS, DPS, or either) between the extrahepatic biliary duct and the upper gastrointestinal tract determined by endoscopy, endosonography, or fluoroscopy. - Clinical success defined as > 50% decrease in bilirubin at 14 days from stent placement. For cholangitis, clinical success is defined as cessation of antibiotics or normalization of levels of blood inflammatory markers within 14 days of stent placement. - Safety, as defined per the ASGE lexicon/Tokyo criteria for endoscopic AEs and divided into early adverse events (within 14 days of index procedure) and delayed AE (> 14 days). - Additional outcomes: t-RBO, BRI, procedure time, and survival/mortality rates.	

*AE* adverse event, *ALP* alkaline phosphatase, *ASGE* American Society of Gastrointestinal Endoscopy, *BRI* biliary reintervention, *CT* computed tomography, *ERCP* endoscopic retrograde cholangio-pancreatography, *EUS* endoscopic ultrasound, *GGT* gamma-glutamyl transferase, *RBO* recurrent biliary obstruction, *US* ultrasound, *MRI* magnetic resonance imaging

^a^Stent occlusion defined as elevation of inflammatory parameters/cholestasis evidence along with biliary dilation on imaging studies or endoscopic findings. Tokyo criteria [20]

^b^Stent migration defined as presence of completely/partially migrated stent at the time of endoscopic reintervention with evident stent dysfunction

^c^Causes of stent occlusions: tumor ingrowth/overgrowth, biliary sludge, food impaction, hemobilia, kinking of CBD to stent). Tokyo criteria [20]

Time to RBO (t-BO) or stent patency is defined as the time from stent placement until the point when symptoms associated with occlusion or migration are observed.

BRI is defined as the need to perform a new therapeutic maneuver on the bile duct due to RBO. A distinction must be made between:
Endoscopic biliary reintervention (e-BRI): endoscopic procedure with the aim of optimizing the transmural BD. It includes stent cleaning, stent change, additional stent insertion, or any other stent-related endoscopic maneuver. For specific information, see Rescue options below.Radiological biliary reintervention (r-BRI): interventional radiological procedure with percutaneous access, with the aim of repermeabilizing the obstructed endoscopic BD.

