#### Statistical analysis

Statistical analysis will be carried out with the R statistical software (version 3.6.2) supervised by the Biostatistics team of our research institute (IDIBELL).

Intention-to-treat and per-protocol analysis will be carried out. All study variables will be presented for stent groups and in total, using descriptive statistics in accordance with the nature of the variable. Thus, continuous variables will be described indicating the number of non-missing observations, mean, standard deviation, minimum, first quartile, median, third quartile, and maximum. The categorical variables will be described indicating the number of non-missing observations and the percentages of the different categories.

Realization of the aim of the study will be analyzed by comparing the cumulative incidence of RBO (as a stent dysfunction parameter) in the LAMS cohort versus LAMS-DPS cohort using a Chi-Square test. The magnitude of the effect will be estimated through an incidence ratio and relative risk with 95% confidence interval. The main analysis will be replicated in an adjusted way using a binomial regression model. Age, sex, oncological status, and comorbidities will be taken as adjustment variables.

Safety will also be evaluated by describing the number and type of AE in each study group, and the incidence will be compared using a chi-square test. In addition, the survival of patients will be analyzed according to the two proposed strategies until the end of follow-up, describing the Kaplan-Meyer curves and comparing them using the LogRank test. The level of statistical significance is established at *p* value < 0.05.

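### Time to RBO (stent patency) stops only at symptoms, although an RBO can be met without them, so a symptom-free RBO counts in the primary endpoint but has no event date

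*Protocol article*

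**What the plan says.** All of the wording at issue is in the Definitions section of the protocol article, including Table 2 and its footnotes.

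- **The clock.** Time to RBO, or stent patency, is "the time from stent placement until the point when symptoms associated with occlusion or migration are observed". No other end date is given.
- **Occlusion (footnote a).** "Stent occlusion defined as elevation of inflammatory parameters/cholestasis evidence along with biliary dilation on imaging studies or endoscopic findings".
- **Migration (footnote b).** "presence of completely/partially migrated stent at the time of endoscopic reintervention with evident stent dysfunction".
- **Primary endpoint (Table 2).** Clinical recurrence is one bullet. Recurrence of cholestasis parameters is another: "Any increase in GGT/ALP or bilirubin from its lowest level post-index procedure". A closing line then adds: "Both WITH evidence of biliary obstruction on imaging (dilation on US/CT/MRI) or endoscopic findings suggesting it".
- **Detection (Clinical evaluation and follow-up).** "If there is clinical suspicion of obstruction or migration of the stent, an upper endoscopy will be carried out".

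Table 2 lists time to RBO among the additional outcomes. The Statistical analysis section names no method for it. That section has a general rule that "continuous variables will be described indicating the number of non-missing observations, mean, standard deviation" and further descriptive statistics, and it names Kaplan-Meier curves and the log-rank test for patient survival: "the survival of patients will be analyzed according to the two proposed strategies until the end of follow-up, describing the Kaplan-Meyer curves". The Statistical analysis plan section defers further analyses and the handling of missing data to a plan that is not shown.

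**The concern.** A time-to-event variable should end on the date of the event that it times. Here the event can be established by blood tests with imaging or endoscopy, while the clock waits for symptoms. A patient can then be an RBO case in the primary comparison and have no time to RBO. Two analysts could handle that patient differently: one would set the time to missing, the other would censor at last follow-up as if the stent had stayed open. Either way, the patency result would rest on fewer events than the primary result, and the two could not be reconciled patient by patient. This matters because the Abstract frames the background question as one of stent patency, and time to RBO is the outcome that carries that name.

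**Working it through.** **1. The definitions applied to individual records.** The patients are illustrative.

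| Record | RBO in the primary endpoint? | Time to RBO as written |
|---|---|---|
| Jaundice at day 60, obstruction then confirmed | Yes | 60 days |
| No symptoms; cholestasis rise and dilated duct on CT at day 95 | Yes under footnote a | None |
| No symptoms; partly migrated stent at reintervention, dysfunction evident from laboratory and imaging findings | Yes under footnote b | None |

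**2. The closing line of the primary endpoint in Table 2.** It can be read in two ways.

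- Each bullet suffices if imaging or endoscopy supports it. The second record is then an RBO without a date.
- Clinical and biochemical recurrence are both required. Symptoms would then always be present and the clock would work, but the second record would be an occlusion under footnote a and not an RBO under Table 2.

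The text is inconsistent on either reading: the first leaves an event undated, and the second sets Table 2 against its own footnote.

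**3. The plan's own figure.** Inputs from Sample size calculation: 20% vs 1%, two-sided 5%, power 80%. With pooled variance under the null hypothesis and p̄ = 0.105:

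n = [1.96·√(2·0.105·0.895) + 0.842·√(0.20·0.80 + 0.01·0.99)]² / 0.19² = (0.850 + 0.347)² / 0.0361 ≈ 39.7, so 40 per arm and 80 in total.

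This reproduces the stated figure (power 80.3% at 40 per arm), and 80 × 1.05 = 84. Time to RBO does not enter the calculation.

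**4. Events that could lose their date.** At 42 per arm, expected RBOs are 42 × 0.20 = 8.4 (LAMS) and 42 × 0.01 = 0.42 (LAMS-DPS). The documents give no share of symptom-free RBO. Over an assumed range:

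- 0%: no event affected.
- 10%: 0.10 × 8.4 = 0.84 LAMS events undated, 7.56 left.
- 30%: 0.30 × 8.4 = 2.52 LAMS events undated, 5.88 left.

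In the LAMS-DPS arm the same shares give 0.04 to 0.13 events.

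**5. Why patients without RBO should be included (for the analysis plan).** Suppose that the general descriptive rule were applied to time to RBO, so that only patients with an event were summarised. Under a constant hazard over one year, λ = −ln(1 − p), and the mean time among patients with an event is 1/λ − (1 − p)/p years.

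- p = 0.20: λ = 0.2231; 4.481 − 4 = 0.481 years = 176 days.
- p = 0.01: λ = 0.01005; 99.499 − 99 = 0.499 years = 182 days.

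A 20-fold difference in risk would appear as 6 days. In 4,000 simulated trials (40 per arm, constant hazards, no deaths, full one-year follow-up), a log-rank test on all patients rejected in about 90%. A rank test on event times alone rejected in about 0.2% and could not be computed in about 66%.

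**The case against.** **Symptom-free RBO may be rare.** Upper endoscopy is triggered by clinical suspicion, only the index procedure and the 24-hour visit require attendance in person, and footnote b requires evident stent dysfunction as well as a displaced stent. This stands, and it limits the size of the problem. It does not remove it: footnote a accepts imaging without endoscopy, and laboratory findings are among the data collected during follow-up.

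**Table 2 may require symptoms.** That is one possible reading of its closing line, but it conflicts with footnote a and so confirms that the passages need reconciling.

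**The analysis plan could set a date.** Additional tests and interventions are to be documented, so it could. It would then have to depart from an explicit protocol definition, and correcting the definition is cleaner.

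**A stronger reading fails.** A reader might infer that the planned summary of time to RBO cannot show a patency difference because only patients with an event have a value. The documents do not support this. No summary specific to time to RBO is planned, naming Kaplan-Meier for survival does not exclude it here, and every time-to-event definition runs from origin to event, with censoring normally left to the analysis plan. The probability of no LAMS-DPS event, 0.99^42 = 66%, is no evidence for it either. It follows from the 1% design rate under any definition, and at an assumed 5% it falls to 0.95^42 = 12%.

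**Conclusion.** The point holds as a mismatch between an event and its clock. Time to RBO ends at symptoms, footnote a lets an RBO be met without them, and Table 2 is ambiguous. A symptom-free RBO is therefore counted in the primary endpoint and undated in the patency outcome.

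The size is unknown and probably small. The range of 0.8 to 2.5 of 8.4 LAMS events rests on the design rate of 20% and on an assumed 10–30% symptom-free share. The outcome is secondary, and neither the sample size nor the primary chi-square comparison uses time to RBO. Because this is a stated definition that mistimes its own event, and not a detail left for later, it should be corrected. How patients without RBO are handled is advice for the analysis plan; the event-only figures show what to avoid, not what the protocol has fixed.

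**What to change.** **In the protocol.** Define time to RBO as the time from stent placement to the earliest qualifying symptom, laboratory, imaging or endoscopic finding of the episode that is confirmed as RBO. Tying the date to the confirmed episode prevents an unrelated earlier enzyme rise from back-dating the event. Reword the closing line of the primary endpoint in Table 2 so that it states whether clinical and biochemical recurrence are alternatives or both required, and align footnotes a and b with it. Every RBO in the primary endpoint then has a date.

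**For the analysis plan.** Give patients without RBO their follow-up time (to death, loss or one year), treat death as a competing event, and present patency by cumulative incidence curves, not by the mean or median of observed event times.

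**Cost.** One reworded definition, one clarified line in Table 2 with its footnotes, and one line in the analysis plan. Laboratory findings, additional tests and interventions are already to be recorded, so no extra patients or visits are needed.

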To clarify the causal relationship and grading of AEs, MEDDEV guidelines will be consulted. Additional file 2 includes all AE definitions based on the MEDDEV 2.12 guidelines (rev 8, July 2019) “Guidelines on medical devices: Clinical investigations: Serious Adverse event reporting under Directives 93/42/EEC and 90/385/EEC”, regarding safety in clinical research with medical devices, which are determined according to the causal relationship and/or severity of AEs.

#### Outcomes

The primary outcome is the rate of RBO after the index procedure, detected during follow-up. As noted above (in the “Definition” section), this is a direct indicator of stent dysfunction, and it is defined as a composite point of either biliary occlusion or stent migration.

The secondary outcomes include technical and clinical success (> 50% decrease in bilirubin at 14 days from stent placement), safety data, and other patient-relevant outcomes (time to RBO, number of reinterventions, procedural time, and mortality rates).

Completed outcomes definitions are presented in Table 2.

#### Sample size calculation

The sample size calculation is based on the primary hypothesis of detecting significant differences in the rates of RBO and BRI between the LAMS and LAMS plus DPS groups (assessing for superiority).
Null hypothesis (H0): πLAMS = πLAMS-DPSAlternative hypothesis (H1): πLAMS ≠ πLAMS-DPS

Based on recently published data, we estimate a recurrent biliary obstruction rate of 20% vs. 1% for the LAMS alone vs. LAMS-DPS groups, respectively up during the follow-up period [13, 19, 22]. To achieve a statistical power of 80% with a two-sided type I error of 5%, a total of 80 patients (40 in each arm) is required to reject the null hypothesis. https://www.stat.ubc.ca/~rollin/stats/ssize/b2.html

Considering a 5% dropout rate, a final sample of 84 patients (42 patients in each arm) is needed.

#### Statistical analysis

Statistical analysis will be carried out with the R statistical software (version 3.6.2) supervised by the Biostatistics team of our research institute (IDIBELL).

Intention-to-treat and per-protocol analysis will be carried out. All study variables will be presented for stent groups and in total, using descriptive statistics in accordance with the nature of the variable. Thus, continuous variables will be described indicating the number of non-missing observations, mean, standard deviation, minimum, first quartile, median, third quartile, and maximum. The categorical variables will be described indicating the number of non-missing observations and the percentages of the different categories.

Realization of the aim of the study will be analyzed by comparing the cumulative incidence of RBO (as a stent dysfunction parameter) in the LAMS cohort versus LAMS-DPS cohort using a Chi-Square test. The magnitude of the effect will be estimated through an incidence ratio and relative risk with 95% confidence interval. The main analysis will be replicated in an adjusted way using a binomial regression model. Age, sex, oncological status, and comorbidities will be taken as adjustment variables.

Safety will also be evaluated by describing the number and type of AE in each study group, and the incidence will be compared using a chi-square test. In addition, the survival of patients will be analyzed according to the two proposed strategies until the end of follow-up, describing the Kaplan-Meyer curves and comparing them using the LogRank test. The level of statistical significance is established at *p* value < 0.05.

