### Methods/design

The BAMPI (*B*iliary *A*pposing *M*etal *PI*gtail) trial is a multicenter, open-label, randomized controlled clinical trial with two parallel groups, and with a 1:1 allocation ratio. Eighty patients with MBO will be scheduled for EUS-BD in seven tertiary Spanish hospitals and will be randomized to the LAMS alone or the LAMS plus DPS group. We hypothesize the addition of a prophylactic DPS through LAMS to be associated with fewer episodes of RBO and, consequently, fewer biliary reinterventions (BRI).

Central ethical approval of the study protocol has been confirmed by the Comité Ético de Investigación Clínica (CEIC) del Hospital Universitari de Bellvitge-IDIBELL (ref approval no. ICPS024/20, on November 2020) and we will not begin recruiting at other centers in the trial until local ethical approval has been obtained.

A checklist with the recommendations for Interventional Trials (SPIRIT) is attached as Additional file 1: SPIRIT-figure with schedule of enrolment, interventions, and assessments in the BAMPI trial (Fig. 1).

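### Neither version of the named chi-square test meets both the stated 5% type I error and the stated 80% power at 40 per arm, and the protocol does not say which version applies

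*Protocol article*

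**What the plan says.** Under Sample size calculation, the protocol article gives the planning rates: "we estimate a recurrent biliary obstruction rate of 20% vs. 1% for the LAMS alone vs. LAMS-DPS groups". For 80% power at a two-sided 5% level it concludes that "a total of 80 patients (40 in each arm) is required to reject the null hypothesis", and then: "Considering a 5% dropout rate, a final sample of 84 patients (42 patients in each arm) is needed". The hypotheses are equality of the two RBO proportions against a two-sided difference.

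Under Statistical analysis, the cumulative incidence of RBO is compared "in the LAMS cohort versus LAMS-DPS cohort using a Chi-Square test". The software is R 3.6.2 and significance is p < 0.05. A continuity correction is neither specified nor excluded.

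Under the section headed Statistical analysis plan, that plan is to be finalized before the database closes, and a deviation concerning the main variable requires an addendum to the protocol.

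**The concern.** With few events, the chi-square distribution is a rough guide to how the test behaves. At the mean of the two planning rates, 10.5%, the expected number of events per arm is 40 x 0.105 = 4.2, below the customary minimum of 5. In that range the corrected and uncorrected tests differ materially, and the nominal 5% and 80% need not hold for either.

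Two things are at stake. One is whether the primary test has the error rate and power that the protocol states. The other is whether the primary conclusion could depend on a software option that the protocol does not fix, in a trial that is open-label.

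**Working it through.** **Inputs from the protocol article.** RBO 20% versus 1%, two-sided 5%, 80% power, 40 evaluable per arm and 42 randomized per arm (Sample size calculation); 1:1 allocation (Methods/design); chi-square test in R, p < 0.05 (Statistical analysis).

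**Input that the protocol does not give.** The type I error depends on the RBO rate common to both arms under the null hypothesis. I take 10.5% = (20% + 1%)/2 as the reference and show 1% to 20%.

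**Step 1: reproduce the sample size.** The uncorrected pooled formula is

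n = [1.960 x sqrt(2 x 0.105 x 0.895) + 0.842 x sqrt(0.20 x 0.80 + 0.01 x 0.99)]² / 0.19²
= [0.850 + 0.347]² / 0.0361 = 39.7, so 40 per arm.

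The stated figure is reproduced. With the continuity correction, n = (39.66/4) x [1 + sqrt(1 + 4/(39.66 x 0.19))]² = 49.6, so 50 per arm. The plan's number therefore belongs to the uncorrected test.

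**Step 2: exact operating characteristics.** For every possible pair of event counts, multiply the two binomial probabilities and sum over the pairs that the test rejects. Power uses 20% and 1%; size uses one common rate in both arms.

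| Test | Power, 40 per arm | Power, 42 per arm | Size at 10.5%, 40 per arm |
|---|---|---|---|
| Chi-square, uncorrected | 90.9% | 92.3% | 5.84% |
| Chi-square, continuity-corrected | 72.9% | 76.5% | 1.4% |
| Fisher's exact | 73.6% | 77.3% | 1.8% |

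Size of the uncorrected test at 40 per arm, by assumed common rate:

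| Common rate | 1% | 5% | 6% | 9% | 10.5% | 15% | 20% |
|---|---|---|---|---|---|---|---|
| Size | 0.1% | 4.3% | 5.1% | 5.9% | 5.8% | 5.4% | 5.1% |

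The maximum is 5.90%, near 9%. At 42 per arm the size at 10.5% is 5.85%. The corrected test first reaches 80% power at 45 per arm (81.1%).

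**Step 3: where the verdicts differ.** Take 4 LAMS events and 0 LAMS-DPS events, 40 per arm; the critical value is 3.84.

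- Uncorrected: 80 x (4 x 40)² / (40 x 40 x 4 x 76) = 4.21, p = 0.040, significant.
- Corrected: (2 - 0.5)² x (2/2 + 2/38) = 2.37, p = 0.12, not significant.
- Corrected with 5 versus 0: (2.5 - 0.5)² x (2/2.5 + 2/37.5) = 3.41, not significant. With 6 versus 0: (3 - 0.5)² x (2/3 + 2/37) = 4.50, significant.

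With 1 LAMS-DPS event the thresholds are 6 and 8. At the planning rates the chance of a table on which the two versions disagree is 90.9% - 72.9% = 18 percentage points at 40 per arm.

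**Step 4: does another test meet both properties?** Unconditional exact tests, with size maximized over the common rate:

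| Test | Power, 40 per arm | Power, 42 per arm | Maximum size | LAMS events needed against 0 |
|---|---|---|---|---|
| Boschloo | 83.5% | 85.9% | 4.8% | 5 |
| Barnard type, pooled Z | 87.5% | 89.3% | 4.8% | 4 |

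**The case against.** The protocol never mentions a continuity correction or Fisher's test, and its sample size comes from the uncorrected formula. The natural reading is therefore the uncorrected test, whose power is well above target. What remains on that reading is a type I error at most 0.9 points over nominal, an ordinary small-sample discrepancy. Whether a correction applies is also a detail that an analysis plan, not shown here, may settle.

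Most of this stands, and it limits the point. A reader might infer that the trial is underpowered at 73%. The documents do not support that: the figure needs a software default that the protocol does not invoke, and it rises to 76.5% if nobody drops out. A reader might also infer that the test exceeds 5% at the event rate that the trial expects. That is not supported either. The trial expects 20% versus 1%, which is the alternative; the 10.5% null rate is an assumption. If the pigtail has no effect and both arms have the LAMS-alone rate of 20%, the expected count is 40 x 0.20 = 8 per arm and the size is 5.1%, close to nominal.

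What does not stand is leaving the matter wholly to the analysis plan. The protocol itself names the test and states both properties, and a choice between corrected and uncorrected would still miss one of them.

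**Conclusion.** The point holds in a limited form. The sample size arithmetic is right, but no version of the named test meets both stated properties at 40 per arm. The uncorrected test exceeds the power target and has a modest type I excess, at most 5.9%, for assumed common rates of about 6% to 20%; at 5% or less it stays below nominal. The corrected test is conservative and falls about 7 points short of 80% power, or 3.5 points if all 42 per arm are evaluable. The more practical consequence is that results such as 4 or 5 events against 0 would be read differently under the two versions.

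This rests on the protocol's planning rates, on independent binomial counts with complete RBO status in each arm, and, for the type I error, on a common rate that the protocol does not give. That R corrects 2x2 tables by default is a property of the software, not a statement in the protocol.

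**What to change.** Under Statistical analysis, replace the chi-square test for the primary RBO comparison with one named unconditional exact test at two-sided 5%, for example Boschloo's, and fix it before database close. Under Sample size calculation, restate the power for that test: for Boschloo, 83.5% at 40 per arm and 85.9% at 42, with maximum size 4.8%. Name only one test. Offering Boschloo or pooled Z as alternatives would bring the ambiguity back, since they disagree at 4 events against 0.

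The cost is a short protocol addendum, which the protocol's own rule on changes to the main variable requires, and somewhat less power than the uncorrected chi-square (83.5% against 90.9%). No patients are added. Merely stating whether the correction applies would remove the ambiguity, but one stated property would still be missed.

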#### Randomization and masking

Patients will be enrolled in this trial by gastroenterologists, surgeons, oncologists, and endoscopists who will evaluate cases in the inpatient wards or outpatient consultation areas. Investigators of each center will be responsible for entering all necessary criteria to an online platform that will generate the randomization sequence, and participants will be randomized with an arbitrary number.

A code list will be generated by our biostatistics department, using R software (v 3.6.3) by randomization with a 1:1 randomization ratio, by blocks, stratified by age (< 65 years old/> 65 years old) and by the presence of liver metastases. The assumption is made that liver metastasis may elevate bilirubin and cholestasis parameters without involving bile duct obstruction. Everyone will be assigned a randomization code along with the treatment that corresponds to it. Once the patient meets the eligibility criteria and has provided informed consent, we will proceed to the allocation of each participant centrally, ensuring allocation concealment, and based on the randomization list. To prevent different subject recruitment rates at the various hospitals from interfering in the development of the study, the entire population will be randomized in blocks of four between the two treatment possibilities.

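### At the protocol's own design rates, the adjusted binomial regression has no finite treatment estimate in about two thirds of trials and too few events for its covariates in the rest

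*Protocol article*

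**What the plan says.** Under Statistical analysis, the cumulative incidence of RBO is compared between arms by a chi-square test. On effect size the protocol states: "The magnitude of the effect will be estimated through an incidence ratio and relative risk with 95% confidence interval". It then adds the adjusted analysis, "The main analysis will be replicated in an adjusted way using a binomial regression model", and lists the covariates: "Age, sex, oncological status, and comorbidities will be taken as adjustment variables". It gives no link function, no interval method, and no provision for an arm without events.

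Under Sample size calculation, "we estimate a recurrent biliary obstruction rate of 20% vs. 1% for the LAMS alone vs. LAMS-DPS groups". On that basis "a total of 80 patients (40 in each arm) is required to reject the null hypothesis", and after the dropout allowance "Considering a 5% dropout rate, a final sample of 84 patients (42 patients in each arm) is needed".

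Under Randomization and masking, allocation is "stratified by age (< 65 years old/> 65 years old) and by the presence of liver metastases". Both factors return under Subgroup analysis. Age is in the covariate list. Liver metastases are not named there, and oncological status is not defined.

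**The concern.** The sample size section and the adjusted model do not fit together. A design that expects 1% RBO in one arm of about 40 patients expects less than half an event there, so the most likely count is zero. A regression of a binary outcome on treatment then has no finite maximum-likelihood treatment coefficient, because the likelihood keeps rising as the coefficient goes to minus infinity. Software returns either a warning or a huge estimate with a meaningless standard error.

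At stake is the adjusted replication of the main analysis. If the trial turns out as designed, that replication will probably give nothing usable. Any substitute not fixed in advance would be chosen in an open-label trial with the results in view. The covariate list also adds variables the randomisation did not use, while leaving unclear whether one that it did use is included.

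**Working it through.** **Inputs.** RBO 20% vs 1%, two-sided 5% error, 80% power, 40 evaluable and 42 enrolled per arm (Sample size calculation); four named covariates (Statistical analysis).

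**1. Reproduce the plan's sample size.** With the pooled-variance formula without continuity correction, n per arm = [1.96·√(2·0.105·0.895) + 0.842·√(0.20·0.80 + 0.01·0.99)]² / 0.19² = 39.7, so 40 per arm. This matches. 80 × 1.05 = 84 also matches.

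**2. Expected events.**
- 40 per arm: 40 × 0.20 + 40 × 0.01 = 8.0 + 0.4 = 8.4.
- 42 per arm: 8.4 + 0.42 = 8.8.

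**3. Chance of an empty LAMS-DPS arm**, (1 − p)^n:
- p = 1%: 0.99^40 = 66.9%; 0.99^42 = 65.6%.
- Other true rates, at 42 per arm: 43% at 2%, 12% at 5%, 1.2% at 10%, 0.5% at 11.8% (an RBO rate with LAMS plus DPS cited in the Discussion).

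**4. Estimability of the adjusted model.** Trials were simulated at 20% vs 1% with treatment plus four binary covariates. The covariates' prevalence (40–50%) and lack of effect are assumptions, since the protocol gives neither. A linear-programming check for separation found no finite maximum-likelihood fit in 66–67% of 1,000 trials per arm size. Almost all of this came from the empty arm.

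**5. Events per coefficient when the arm is not empty.** Count treatment plus four single-term covariates, so 5 coefficients.
- 40 per arm: expected LAMS-DPS events given at least one = 0.4 / (1 − 0.669) = 1.2, so the total is 9.2 and 9.2 / 5 = 1.8.
- 42 per arm: 0.42 / (1 − 0.656) = 1.2, so the total is 9.6 and 9.6 / 5 = 1.9.
- Higher DPS rates help little (42 per arm, all trials): at 5%, 10.5 / 5 = 2.1; at 11.8%, 13.4 / 5 = 2.7.

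If oncological status or comorbidities take several terms each, these ratios fall further.

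**6. What still works with an empty arm.**
- Chi-square, 8/40 vs 0/40: statistic 8.89, p = 0.003 (0.009 with Yates correction; Fisher 0.005).
- Relative risk: the estimate is 0 and the Wald interval on the log scale is undefined, but the score interval for 0/42 vs 8/42 runs from 0 to about 0.45. Adding 0.5 to the cells gives 0.004 to 0.99, so the choice of method matters.
- Risk difference, 8/40 vs 0/40: 20%, Miettinen–Nurminen 95% CI 10.3% to 34.9%.

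**The case against.** The strongest reply is that the primary inference does not depend on this model. The chi-square test is computable with an empty arm, and the regression only replicates it. That stands, and it limits how serious the point is.

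A reader might infer that the planned relative risk interval also fails. The protocol does not support that. It fixes no interval method, only the Wald log interval breaks down, and the choice of method can properly be left to the statistical analysis plan.

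A reader might also infer that an empty arm is the likely result whatever the truth. That holds only near the assumed 1%. The Discussion cites 11.8% RBO with the added pigtail in one retrospective study, and a slightly higher RBO rate with it in the group's own study. At such rates separation is rare, though the model remains overloaded.

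Nor can it be said that liver metastases have been left out. Oncological status may cover them and they are a planned subgroup, so this is an ambiguity.

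Finally, the statistical analysis plan is due before database close and may add sensitivity analyses. But the protocol says that plan will include the analyses described, so it inherits this model and covariate list unless they are changed.

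The remedy has limits too. Treatment plus two factors on 8.4 events is 8.4 / 3 = 2.8 events per coefficient, still few. Penalisation keeps the estimate finite; it does not make the data rich.

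**Conclusion.** The point holds for the adjusted model and should be fixed. At the protocol's own rates, the stated regression has no finite ordinary maximum-likelihood treatment estimate (logit or log link) in about two thirds of trials, and under 2 events per coefficient in the remainder. The two-thirds figure rests on the 1% assumption. The overload does not: across DPS rates from 1% to 11.8% the model never reaches 3 events per coefficient, with the LAMS rate held at 20% and one term per covariate. The chi-square test is sound in this respect, so the point does not threaten the primary result.

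**What to change.** Before the database closes, amend the adjusted analysis as follows.

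- Replace the four-covariate model with a Firth-penalised model, or a stratified analysis, on treatment plus the two randomisation factors: age (<65 / ≥65, so that a patient aged exactly 65 has a category) and liver metastases.
- Name liver metastases explicitly instead of relying on the undefined oncological status.
- Move sex, comorbidities and other oncological variables to exploratory analyses.
- Name a score interval for the relative risk, and report the risk difference with its score interval alongside. Making the risk difference the main measure would be a preference; no error requires it.

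The cost is wording in the protocol and analysis plan. Sample size, conduct and data collection do not change. The downsides are fewer covariates in the adjusted model and, if Firth logistic regression is chosen, an adjusted odds ratio beside an unadjusted relative risk; the report should say that the two are not directly comparable.
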